### Participants

The subjects are introduced to the trial, and those who are interested to know more are invited via email, phone call, SMS, or social media (Telegram or WhatsApp) to the study center, where the study investigator explains the study in detail to the subjects. After the clarifications have been provided, the subject will be asked to voluntarily sign the consent form (Supplementary Material, Table S3), and the first appointment will be booked. In the first appointment, the consented subjects undergo screening procedures for the study under an endocrinologist according to the ADA guidelines. The eligible subjects will be enrolled in the trial and randomized to the appropriate study groups. The screening period is planned for 12 months and will continue until 84 participants are randomized in the study.

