### Sample size

The sample size was determined based on the ability to detect a mean effect of FPG between the supplement and placebo groups for each supplement (curcumin or zinc), separately.

By using the following formula, the maximum sample size for curcumin group based on the trial by Chuengsamarn et al. [26] and zinc group based on the trial by Ranasinghe et al. [40] was determined to be 8 ($$ {\overline{X}}_1 $$ = 3.64, $$ {\overline{X}}_2 $$ = − 7.54, *S*_1_ = 8.17, and *S*_2_ = 7) and 19 ($$ {\overline{X}}_1 $$ = + 16, $$ {\overline{X}}_2 $$ = + 3, *S*_1_ = 12.8, and *S*_2_ = 15.3), respectively (*α* = 0.05, significance; *β* = 0.2, power). Then, the maximum sample size was considered as the final sample size, which is sufficient to evaluate the main effects. According to an expected 10% loss at follow-up, 84 subjects (21 participants in each group) will be recruited, finally.

$$ {n}_1=\frac{\left({S}_1^2+{S}_2^2\right){\left({Z}_{1-\frac{\alpha }{2}}+{Z}_{1-\beta}\right)}^2}{{\left({\overline{X}}_1-{\overline{X}}_2\right)}^2} $$

In the formula above, *S*^2^ and $$ \overline{X} $$ show the variance and the mean effect for FBS in the placebo and treatment groups, respectively. Also, for a more accurate calculation of the sample size, the WinPepi statistical program (version 11.4: Abramson, 2011) was performed.

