### Randomization and blinding

The randomization of the participants for this study will be conducted using the method of block randomization with a block size of 4 using a computer-generated random number sequence by one of the research staff (who is an independent statistician and not available to the study investigators or the study staff). Then, the allocation concealment will be conducted assigning the unique codes in order to prevent “selection bias,” and it will be maintained by the pharmacist who is a research staff not involved during the study (the pharmacist is involved only with the dispensing of the investigational products). After checking the inclusion and exclusion criteria and the baseline measurements by two investigators, the eligible participants will be given consecutive numbers, which will be forwarded to the pharmacist who will dispense the interventional product. The pharmacist will open the sealed envelope (that is given by the independent statistician containing the treatment code) after the final data analysis and/or an emergency situation. All the assessments in the trial will be made by the investigators blinded to the treatment allocation. In the event of an emergency situation where being aware of the treatment allocation is critical, the pharmacist will be accessed to unblinding envelopes provided for each participant. Further assessment and required medical or legal interventions will be carried out according to the case. The emergency unblinding and the reason should be recorded in the case report form. The treatment code would be communicated to the medical personnel in charge of the treatment but should not be recorded or verbally disclosed in any of the study documents or to the patient. Since this is a double-blinded study, the investigators, participants, and those involved in the study will not be informed about the type of supplement used except the research staff. The supplements will be delivered to the participants according to the allocation on the 1st, 30th, and 60th days.

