### Laboratory investigations

Blood samples (12 ml) of all participants will be collected after 12 h of overnight fasting at the baseline and at the end of the study. The samples will be collected into two different tubes (in the tube without anticoagulant and in EDTA tubes) and centrifuged to obtain the serum or plasma. The serum samples (3 ml) will be stored at − 80 °C. The plasma and the remaining serum will be used to determine the FPG, 2hpp (glucose oxidase/peroxidase method, BioSystem, Spain), HbA1c (HPLC, TOSOH, Japan), TG (glycerol phosphate oxidase/peroxidase method, BioSystem, Spain), TC (cholesterol oxidase/peroxidase method, BioSystem, Spain), HDL-C (direct method, BioSystem, Spain), SOD (colorimetric (420 nm) method, ZellBio GmbH, Germany), TAC (colorimetric (570 nm) method, ZellBio GmbH, Germany), MDA (colorimetric (535 nm) method, ZellBio GmbH, Germany), ALT, AST (IFCC method, BioSystem, Spain), serum insulin (enzyme-linked immunosorbent assay (ELISA) kit, Monobind, USA), serum zinc (flame atomic absorption spectrometry method (Ziest Chem Diagnostics kit, Iran), serum IL-1B (human IL-1β (ELISA kit), BE58011, IBL, Hamburg, Germany), and serum hs-CRP )ELISA kit, EU59131, IBL, Hamburg, Germany). At least 1 ml of random urine specimen (the fasting state is not necessary for urine collection) will be taken at the baseline and at the end of the study for the measurement (urine zinc by flame atomic absorption spectrometry method (Ziest Chem Diagnostics kit, Iran; normal range 15–150 μg/dl). All biochemical tests except IL-1B, hs-CRP, SOD, TAC, and MDA will be conducted immediately after sampling.

The following formula will be used to calculate VLDL and LDL-C:
VLDL = TG (mg/dl)/5 (this formula is valid only when TG are ≤ 400 mg/day)LDL-C = TC (mg/dl) − HDL-c (mg/dl) − TG (mg/dl)/5; Friedewald formula [50].

The homeostasis model of assessment 2 (HOMA-2) calculator will be downloaded from the University of Oxford and used to calculate IR, S%, and BCF% (http://www.dtu.ox.ac.uk/).

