### Statistical analysis

Before statistical analysis, all data will be reviewed to check the accuracy and completeness. The primary analysis will be conducted on the intention-to-treat (ITT) population. Per-protocol (PP) and sensitivity analyses may be conducted as appropriate. The normality of data will be checked by the Kolmogorov-Smirnov test. The variables will be reported as mean ± SD or median (*Q*). The percentage changes for each variable will be separately reported and calculated by the following formula:
$$ \left[\left(E-B\right)/B\times 100\right], $$

where *E* and *B* are the end value and the baseline value of the variable, respectively.

According to the normality assumption, the significant changes between the groups will be assessed through a one-way analysis of variance (one-way ANOVA) with post hoc (LSD) analysis or Kruskal-Wallis. Changes from the baseline to post-intervention within the groups will be illustrated through a paired *t* test or Wilcoxon signed-rank test. The qualitative and quantitative variables in the two groups will be compared using the chi-square and *t* test, respectively. If necessary, the analysis of covariance (ANCOVA) will be used to control the potential confounding variables.

All analyses will be performed using a statistical software package (SPSS), version 22.0 (SPSS, Inc., Chicago, IL, USA), or NCSS2020. Statistical significance will be determined at *p* < 0.05.

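### The planned one-way ANOVA ignores the randomisation blocks of four, which may forgo some precision; the loss depends on a within-block correlation the protocol does not give

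*Protocol article*

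**What the plan says.** Four passages of the protocol article matter.

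- **Randomization and blinding:** allocation is done "using the method of block randomization with a block size of 4 using a computer-generated random number sequence". Study design describes four parallel arms in a 2 × 2 factorial, Sample size sets 21 participants per arm, and no strata are described.
- **Participants:** "The screening period is planned for 12 months and will continue until 84 participants are randomized in the study". Trial status gives January to December 2020.
- **Laboratory investigations:** "All biochemical tests except IL-1B, hs-CRP, SOD, TAC, and MDA will be conducted immediately after sampling". Part of the serum is stored frozen.
- **Statistical analysis:** "the significant changes between the groups will be assessed through a one-way analysis of variance (one-way ANOVA) with post hoc (LSD) analysis or Kruskal-Wallis". ANCOVA is held in reserve for possible confounders, none of which is named. Neither block nor enrolment period appears in any model.

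**The concern.** With four equal arms and a block size of four, each block holds one participant from each arm, enrolled within a short period. Whatever block members have in common cancels from every comparison between arms. A one-way ANOVA does not use this: variation between blocks goes into its residual mean square, so the standard error it reports can exceed the true standard error of the difference.

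Some shared variation is plausible. Of the 18 parameters in the primary objective, only four (TAC, MDA, IL-1B and hs-CRP) are exempt from immediate testing. The other 14, including FPG, the sample-size outcome, are measured, or derived from values measured, as participants accrue. Everyone also receives a weight-loss diet and advice to walk or cycle, so season could affect the 90-day change itself.

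At stake is precision: wider intervals and somewhat lower power than the randomisation would support, with 21 participants per arm.

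The reserve ANCOVA does not obviously cover this. It is aimed at confounders, and a block balanced across arms is not one. The reason to model it is precision.

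**Working it through.** **1. The plan's own figure.** Inputs from Sample size: two-sided α = 0.05, β = 0.2; zinc means +16 and +3, SDs 12.8 and 15.3; curcumin means 3.64 and −7.54, SDs 8.17 and 7. The formula is n = (S₁² + S₂²)(z₀.₉₇₅ + z₀.₈₀)² / (difference)².

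- Zinc: (163.84 + 234.09) × 7.849 / 13² = 18.48, so 19.
- Curcumin: (66.75 + 49) × 7.849 / 11.18² = 7.27, so 8.
- Losses: 19 × 1.1 = 20.9, so 21 per arm and 84 in all.

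The stated figures reproduce. They come from an unblocked two-group formula.

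**2. Blocks.** 84 / 4 = 21 blocks; 365 / 21 ≈ 17 days per block.

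**3. Effect on the standard error.** Let ρ be the share of the variance of the change that is common to a block. With complete blocks, the one-way residual mean square has expectation σ²(1 − ρ) + σ²ρ = σ², while the true variance of a difference between arms depends on σ²(1 − ρ) only. The reported standard error is therefore too large by the factor 1/√(1 − ρ).

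**4. Break-even.** Fitting block as a fixed effect lowers the error degrees of freedom from 80 to 60. The critical values are t₀.₉₇₅ = 1.990 (80 df) and 2.000 (60 df). The interval narrows only if ρ exceeds 1 − (t₈₀/t₆₀)² ≈ 0.01.

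**5. Size and power.** This simulation used 100,000 trials per setting, 21 complete blocks of four, and total SD fixed at √(397.93/2) = 14.1. ρ is an assumption, shown over a range. The power columns are for one LSD pair, without and then with block. The difference of 13 is the protocol's zinc effect (13/14.1 = 0.92 SD); 8 is a smaller effect, for illustration.

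| ρ | SE too large by | Size, one-way F | Size, LSD pair | Power, difference 13 | Power, difference 8 |
|---|---|---|---|---|---|
| 0 | 0% | 5.0% | 5.1% | 84.0 → 83.7% | 44.3 → 44.1% |
| 0.02 | 1.0% | 4.7% | 4.7% | 84.1 → 84.3% | 44.3 → 44.7% |
| 0.05 | 2.6% | 4.1% | 4.4% | 84.4 → 85.4% | 44.1 → 45.8% |
| 0.10 | 5.4% | 3.5% | 4.1% | 85.2 → 87.3% | 44.0 → 47.9% |
| 0.20 | 11.8% | 2.2% | 3.0% | 86.6 → 90.8% | 43.9 → 52.6% |
| 0.30 | 19.5% | 1.3% | 2.0% | 87.7 → 93.8% | 43.2 → 57.9% |

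With block in the model, size was 4.8% to 5.1% throughout. The overall F test can gain slightly more than a pair does: for a difference of 8 at ρ = 0.10, its power went from 40.6% to 46.1%.

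**6. Incomplete blocks.** With 8 of 84 participants lost (about the planned 10%):

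- Block as a fixed effect: intervals 2.4% wider at ρ = 0, about equal at 0.05, 3.0% narrower at 0.10 and 8.5% narrower at 0.20.
- Block as a random effect, 0.92 SD pair: power 81% to 83% at 0.05, 81% to 84% at 0.10 and 82% to 87% at 0.20. At ρ = 0 the rejection rate under no effect was 6.0% without block and 6.3% with it, in the same runs. The one-way test is exact there, so its excess over 5% is simulation error; the informative figure is the 0.3-point difference.

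None of these runs included the baseline value, so any gain from it would be extra.

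**The case against.** The strongest objection is that ρ appears nowhere in the protocol. If it is zero, the planned test has exactly its nominal size and nothing is lost. **This stands.** A reader might infer that the tests are in fact conservative; the documents support only the conditional statement.

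The assay argument is also weaker than it looks. A reader might infer that all assays are run sample by sample, but five markers are exempt from immediate testing, and the article does not say how those are batched. For the rest, a block spans about 17 days, so its members will often be tested on different days. Day-to-day run variation then falls largely within blocks, where no block term can remove it. An offset common to baseline and day 90 cancels from the change. Only season and slow drift remain. **This stands** and favours the lower end of the range. Anthropometry, blood pressure and the questionnaires involve no assay, so for them only season or other calendar effects could be shared.

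A reader might also infer that real effects will be missed. At the protocol's zinc effect, a pair gains only about 1 point at ρ = 0.05 and 2 at 0.10. For a main effect of that size (42 against 42), power is 98.7% without block and 98.9% or 99.2% with it. Missed effects are not shown at the effects the trial was sized for.

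Finally, it can be said that a block term belongs in an analysis plan that is not shown. As an omission it would be no finding. Here, however, the article names its test, and that test leaves the blocks out, so comment on the choice is fair. The article contains no contradiction on this point: an unblocked sample size and an unblocked test agree with each other.

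**Conclusion.** The point holds as a minor and conditional matter of efficiency. The design yields 21 blocks of one participant per arm, and the stated test does not use them. If block members share variation in the 90-day change, standard errors are too large by 1/√(1 − ρ) and the tests are conservative. For pairwise comparisons the cost is nil at ρ = 0, about 1 to 2 points of power at 0.05, about 2 to 4 at 0.10, and larger only at 0.20 or more, for which the documents give no support.

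These sizes assume normal outcomes and a block effect common to all four arms, with complete blocks except in the check with losses. They do not cover the Kruskal-Wallis branch.

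A reader might infer that the planned analysis is invalid or the sample size wrong. Neither follows: any error is on the safe side for type I error, and N stays at 84.

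**What to change.** For approximately normal continuous outcomes, replace the one-way ANOVA of changes with a linear mixed model containing treatment terms, the baseline value and randomisation block as a random effect, with Satterthwaite degrees of freedom. State in advance that the block term is dropped if its variance is estimated at zero. Fix this before unblinding. The comparisons between arms can still be read from this model.

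The random form is preferable to a fixed block effect. It copes with blocks made incomplete by losses, whereas fixed blocks widened intervals by about 2% at ρ = 0 with 10% lost.

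The cost is a slightly more complex model and the block number from the randomisation list; no new data or participants are needed. If blocks do not differ, the block term brings little or no gain.

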## Method

### Study design

The flow chart of the study design and the schedule of enrollment, interventions, and assessments are shown in Figs. 1 and 2, respectively. The participant will be randomized in a 2 × 2 factorial design into four parallel treatment groups: (1) curcumin group (Cur/P.Zn), curcumin supplement + placebo for zinc; (2) zinc group (Zn/P.Cur), zinc supplement + placebo for curcumin; (3) zinc + curcumin group (Zn/Cur), zinc supplement + curcumin supplement; and (4) placebo group (P.Zn/P.Cur), placebo for curcumin and zinc. The follow-up duration will be 3 months (90 days).

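### A 2 × 2 factorial trial is given a four-group one-way analysis, so neither the main effects named in the sample size section nor the curcumin-by-zinc interaction is estimated

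*Protocol article*

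**What the plan says.** The Study design section states the structure: "The participant will be randomized in a 2 × 2 factorial design into four parallel treatment groups". The cells are curcumin alone, zinc alone, both, and neither, with a matching placebo for each supplement not given.

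The Sample size section works on fasting plasma glucose (FPG). It compares supplement with placebo for curcumin and for zinc separately, takes the larger result, and describes it as a number "which is sufficient to evaluate the main effects". After an allowance for loss to follow-up, "84 subjects (21 participants in each group) will be recruited, finally".

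The Statistical analysis section then says that changes between groups will be "assessed through a one-way analysis of variance (one-way ANOVA) with post hoc (LSD) analysis or Kruskal-Wallis". It adds paired tests within groups, and ANCOVA if needed for confounders. A further sentence reads "The qualitative and quantitative variables in the two groups will be compared using the chi-square and" a t test, without saying which two of the four groups are meant. No two-factor model, no pooled supplement-v-no-supplement comparison and no interaction term appears anywhere in the article.

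The Hypothesis section is about co-supplementation improving outcomes. The Introduction and the Abstract's discussion speak of an expected synergistic effect.

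**The concern.** A one-way ANOVA treats the four cells as levels of a single unordered factor. Its omnibus test asks whether any cell differs from any other, and LSD then compares cells two at a time. Neither step estimates the effect of zinc averaged over curcumin, or of curcumin averaged over zinc. These averages are the main effects for which a factorial is usually chosen and which the Sample size section names. Each LSD pair for a supplement uses two of the four cells, so half of the participants who carry information on that supplement contribute nothing to the comparison except to the error variance.

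The interaction is also absent, and Kruskal-Wallis offers no test of it. A reader who expects synergy is left with a set of pairwise p-values. A pattern in which the combination differs from placebo while the single supplements do not is not evidence of interaction.

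This is not a detail left to a later document. The article names a specific model, and that model does not match the design it describes.

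**Working it through.** **Inputs (Sample size section).** Zinc: mean changes +16 and +3 (difference 13 mg/dl), SDs 12.8 and 15.3. Curcumin: 3.64 and −7.54 (difference 11.18), SDs 8.17 and 7. α = 0.05, two-sided by the formula; power 80%; 10% loss.

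**Step 1: reproduce the plan's figures.** n = (S₁² + S₂²)(1.960 + 0.842)² / (difference)².
- Zinc: (163.84 + 234.09) × 7.849 / 169 = 18.48, so 19.
- Curcumin: (66.75 + 49) × 7.849 / 124.99 = 7.27, so 8.
- 19 × 1.1 = 20.9, so 21 per group; 21 × 4 = 84.

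The stated 8, 19, 21 and 84 all reproduce. The formula is for two groups and its result is used per cell. The 80% therefore belongs to one pairwise cell contrast, although the text speaks of main effects.

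**Step 2: precision of each comparison.** Zinc inputs, SD = √((12.8² + 15.3²)/2) = 14.1, 19 completers per cell, 4 × 19 − 4 = 72 error df, t(0.975) = 1.993. Power is from the noncentral t.

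| Comparison | SE | 95% CI half-width | Power at 13 mg/dl | Power at 6.5 mg/dl | Detectable at 80% |
|---|---|---|---|---|---|
| One LSD pair, 19 v 19 | 14.1√(2/19) = 4.58 | 9.1 | 80.0% | 29% | 13.0 |
| Main effect, 38 v 38 | 14.1√(2/38) = 3.24 | 6.5 | 97.7% | 51% | 9.2 |
| Interaction (difference of differences) | 2 × 14.1/√19 = 6.47 | 12.9 | 51% | 17% | 18.4 |

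The half-effect of 6.5 mg/dl and both interaction sizes are assumptions; the article gives none. The main-effect row assumes no large interaction.

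**Step 3: the omnibus F test.** Noncentral F with 3 and 72 df:
- Zinc alone acts and adds 13 in both zinc cells: 92%.
- Zinc alone acts and adds 6.5 in both: 34%.
- Only the combination works, by 13: 82%.

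**Step 4: the case against the main effects.** If only the combination works, by 13 mg/dl, each main effect averages 13 and 0, which is 6.5, and has 51% power. The direct combination-v-placebo pair has 80%.

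**Step 5: size needed for the interaction.** n per cell = 4 × SD² × 7.849 / (interaction)². For 13 mg/dl: 4 × 198.97 × 7.849 / 169 = 36.96, so 37 per cell (148 evaluable). For 6.5 mg/dl it is 148 per cell.

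**The case against.** The strongest reply is that the analysis matches the arithmetic of the sample size even if it does not match the label. Nineteen was applied per cell and LSD tests cell against cell, so each zinc pair has the planned 80%, and the omnibus test has 92% in the plan's own zinc scenario. The one-way ANOVA is also a valid comparison of randomised groups. This stands. A reader might infer that the trial cannot detect the effects for which it was sized; the figures do not support that.

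A reader might also infer that the trial sets out to claim an interaction. The documents do not go so far. The objectives compare mean changes between groups, and the hypothesis says only that co-supplementation improves outcomes. Synergy is an expectation voiced in the Introduction and Abstract, in part tied to the diet that all arms receive.

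Third, making the two main effects the only principal results would sideline the hypothesis, and would do worse if only the combination works (51% against 80%). This also stands and shapes the fix.

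Fourth, the two groups in the t-test sentence might be the pooled margins, supplement yes and no, in which case the t test would be a main-effect comparison. The text does not say so. The sentence is undefined, not demonstrably wrong.

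Finally, planned contrasts within a four-cell ANOVA could recover the factorial effects. The plan names only LSD.

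**Conclusion.** The mismatch is real. The design is factorial and the size is justified by main effects, yet the named analysis estimates neither a main effect nor the interaction. The loss lies in the target and the precision of the estimates. On the zinc inputs, the 95% CI half-width for a supplement's effect is 9.1 mg/dl from an LSD pair and 6.5 mg/dl from a main effect, about 29% narrower (1 − 6.5/9.1) with the same participants. Power at 13 mg/dl is 80% against about 98%. These figures rest on SD 14.1, 19 completers per cell and no large interaction.

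As planned, any statement on synergy would rest on comparing pairwise p-values, which is not a test of interaction. The factorial model would supply the right estimate but not a reliable test: power is about 51% for an interaction as large as the whole assumed zinc effect and 17% for half of it.

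**What to change.** In the Statistical analysis section:

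1. Replace the one-way ANOVA/LSD/Kruskal-Wallis sentence with a two-factor linear model: curcumin (yes/no), zinc (yes/no), their interaction, and the baseline value of the outcome.
2. Report as principal results, each with a 95% CI, the two main effects and the pre-specified contrast of the combination group with the double-placebo group, which addresses the Hypothesis section. Show the four cell means beside them.
3. Report the interaction as an estimate with its 95% CI, state that the trial is underpowered for it, and state that no synergy will be claimed from pairwise p-values.
4. Name the groups in the t-test and chi-square sentence, or remove it.

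The cost is wording only: no more participants, visits or assays. The change should be made before unblinding, since a later choice between cell-wise and factorial analysis could be driven by the data. The downside is that main effects average over the other factor and can hide an effect confined to the combination. This is why the combination contrast stays principal and the cell means are shown.

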### Hypothesis

Curcumin and zinc co-supplementation will significantly improve the serum levels of biochemical parameters, anthropometric data, HRQOL, PA, and BP in prediabetic patients.

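### The main between-group test ignores the baseline value, its form depends on a normality pre-test, and ANCOVA is an unspecified conditional extra, so no single primary model is fixed

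*Protocol article*

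**What the plan says.** The primary objective compares mean changes in a long list of biochemical parameters between the groups. The Outcomes section has all primary and secondary outcomes taken at baseline and at day 90.

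The Statistical analysis section sets out the tests:

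- "The normality of data will be checked by the Kolmogorov-Smirnov test". Depending on the result, changes are compared between groups by one-way ANOVA with LSD post hoc tests, or by Kruskal-Wallis. Neither includes the baseline value as a covariate.
- "If necessary, the analysis of covariance (ANCOVA) will be used to control the potential confounding variables". No trigger, covariate list or restriction to pre-randomisation values is given, and nothing says whether the adjusted or the unadjusted result is primary.
- "The percentage changes for each variable will be separately reported and calculated by the following formula". This concerns reporting, not testing.

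The Hypothesis section states that co-supplementation "will significantly improve the serum levels of biochemical parameters, anthropometric data, HRQOL, PA, and BP in prediabetic patients". Weight (within the anthropometric data) and physical activity (PA) are therefore outcomes that treatment is expected to change.

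**The concern.** Three features of the stated method work against the trial.

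1. **Lost precision.** A baseline value of every outcome is available at no extra cost but is not used as a covariate. With about 19 evaluable participants per arm, that matters.
2. **More than one candidate p-value.** The form of the main test depends on a pre-test of the same data, and an adjusted analysis may or may not follow. If the choice is made once results are known, the 5% error rate no longer holds.
3. **Open covariate set.** The wording allows any variable regarded as a confounder, including day-90 weight or activity. Adjusting for a variable that treatment has changed removes part of the treatment effect from the estimate.

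**Working it through.** **Inputs from the Sample size section.** Two-sided alpha 0.05, power 80%. Zinc: mean effects +16 and +3 (difference 13 mg/dl in fasting glucose), SDs 12.8 and 15.3. Curcumin: 3.64 and −7.54 (difference 11.18), SDs 8.17 and 7.

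**Inputs assumed.** The SDs are taken as SDs of change. Variances at baseline and day 90 are taken as equal. The baseline to day-90 correlation r is not in the article, so a range of 0.3 to 0.9 is used.

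**Step 1: reproduce the plan's figures.** n = (S1² + S2²)(1.960 + 0.842)² / difference², with (1.960 + 0.842)² = 7.849.
- Zinc: (163.84 + 234.09) × 7.849 / 169 = 18.48, so 19.
- Curcumin: (66.75 + 49) × 7.849 / 124.99 = 7.27, so 8.

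Both match the article, and 19 × 1.10 = 20.9 gives its 21 per group. The sample size is not disputed here.

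**Step 2: relative precision.** With common variance σ², the change score has variance 2σ²(1 − r) and the baseline-adjusted day-90 value has σ²(1 − r²). The ratio is (1 + r)/2.

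**Step 3: pairwise power at 19 per arm.** The root mean square SD is √(397.93/2) = 14.1. The noncentrality for the change score is 13 / (14.1 × √(2/19)) = 2.84; for ANCOVA it is divided by √((1 + r)/2). Power is from the noncentral t distribution with two-arm degrees of freedom.

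| Analysis | Variance ratio | Power |
|---|---|---|
| Change score | 1.00 | 79% |
| ANCOVA, r = 0.3 | 0.65 | 93% |
| ANCOVA, r = 0.5 | 0.75 | 89% |
| ANCOVA, r = 0.7 | 0.85 | 85% |
| ANCOVA, r = 0.9 | 0.95 | 81% |

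The normal approximation gives figures 1 to 2 points higher (81% for the change score; 94%, 91%, 87% and 83% for ANCOVA).

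**Step 4: choosing between results.** Four arms of 19 were simulated with normal data and no treatment effect, 4,000 runs per value of r. Each test alone rejected in about 5% to 6%. Taking the smaller of the ANOVA and ANCOVA p-values rejected in 9.0%, 7.0% and 7.2% at r = 0.3, 0.5 and 0.7.

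**Step 5: the normality switch.** With 19 lognormal observations (log SD 0.5 to 1.0), the plain Kolmogorov-Smirnov test detected the skew in 1% to 16% of samples, and the Lilliefors version in 34% to 77%. The article does not say which version applies, or whether it is applied to values, changes or residuals. The method used for a skewed marker therefore depends on an unstated detail.

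**Step 6: a skewed marker.** For lognormal data (log SD 0.8, r = 0.6, log effect −0.35, 19 per cell), the four-group test rejected in 27% with Kruskal-Wallis on raw change, 39% with ANOVA of log change and 47% with ANCOVA on logs. On the same log scale and with the same contrast, baseline adjustment accounts for about 8 points; the rest of the gain comes from the log scale. These data suit the log model by construction.

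**The case against.** The strongest reply is that nothing here is invalid. An unadjusted comparison of changes is unbiased under randomisation and holds its 5% level, and at the article's own inputs it already has about 80% power. The covariate list and the trigger for ANCOVA could sit in an analysis plan that is not shown. The size of the gain rests on a correlation the article does not give.

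Much of this stands. The precision point concerns efficiency, not bias. The reply does not remove the finding, because the article itself commits to an unadjusted, data-selected main test and makes adjustment conditional. That is a stated choice, not a detail left out.

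Several stronger readings are tempting, but the article does not support them:

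- *That adjustment for post-baseline variables is planned.* It is only not excluded. Age, sex and baseline values are equally possible covariates.
- *That treatment is expected to change dietary intake.* The Hypothesis section does not list it; the secondary objective only compares it.
- *That percentage change is the basis for testing.* It is only reported, so its failure at a zero baseline is a minor reporting matter.
- *That ANCOVA can never be less precise.* This holds in large samples. In simulation at 19 per arm the variance ratio was 1.00 at a correlation of 0.95 and 1.02 at 0.98.
- *That rejection for a skewed marker would rise from about 28% to 65% through adjustment.* That contrast also changes the scale and replaces the four-group test by a factorial main effect.

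**Conclusion.** The point holds as a worthwhile improvement, not as an error that invalidates the trial. The main test is valid but generally less precise than ANCOVA on the outcome's own baseline. At the zinc planning inputs with 19 per arm, the gain is about 14, 10, 6 and 2 percentage points of power at correlations of 0.3, 0.5, 0.7 and 0.9, and none as the correlation nears 1. These figures assume equal variances at the two visits and that the planning SDs describe change.

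The lack of a fixed primary model is the second part. If the better of the adjusted and unadjusted results were taken, false positives would be about 7% to 9% per outcome. The article does not say that this would be done; its wording leaves it possible, as it does adjustment for day-90 weight or physical activity.

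**What to change.** Amend the Statistical analysis section as follows:

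1. Make the single primary analysis of each continuous outcome an ANCOVA of the day-90 value on randomised treatment, with the same outcome's baseline value as covariate.
2. Name any further covariates in advance and limit them to pre-randomisation variables.
3. Replace the Kolmogorov-Smirnov switch with a log transformation fixed in advance for skewed markers (such as triglycerides, insulin, hs-CRP and IL-1B), and keep rank tests as a sensitivity analysis.
4. Label any analysis that adjusts for post-baseline change, for example in weight or activity, as exploratory.

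The cost is a change of wording and one degree of freedom per model. The baseline values are already collected, so no new data, visits or participants are needed.
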